#### Verification of Opioid Status and Dose

Opioid use and dose were verified by review of pharmacy and medical records. Opioid doses were converted to daily morphine equivalents using a conversion calculator as previously reported [15-17]. The opioid status was biochemically verified with a urine toxicology screen.

#### Occurrence and Risk of Opioid Misuse

The occurrence and risk for opioid misuse was assessed using 3 instruments. The Alcohol, Smoking, and Substance Involvement Screening Test (ASSIST) was administered. The ASSIST is validated [18] and used in the National Institute on Drug Abuse Quick Screen [19]. The Prescribed Opioid Difficulties Scale [20] was used to assess for substance use disorders associated with use of prescribed opioids [21]. The Opioid Risk Tool is a brief questionnaire that is validated [22] and was used to assess the risk of opioid misuse.

#### Symptoms of Opioid Withdrawal

Symptoms of opioid withdrawal were assessed using the Clinical Opiate Withdrawal Scale, which is an observer-rated instrument [23,24].

#### Opioid Craving

Opioid craving was assessed using responses (0 to 100 on a visual analog scale) to 3 questions: (1) How much do you crave opioids? (2) How often do you think about the next dose? and (3) How strong is your urge to take more medication than prescribed? This approach is validated [25] and was used to assess opioid craving [26-28].

#### Pain Intensity

Pain intensity was assessed using the 11-point verbal pain rating scale. The validity of the verbal pain rating scale is well established [29-31].

#### Michigan Body Map

The Michigan Body Map (MBM) is a self-report measure to assess body areas where pain is experienced. The MBM has demonstrated utility, reliability, and construct validity [32,33]. The MBM measure has been used to assess pain in a broad range of clinical settings [34-41].

#### Pain-Related Psychosocial Functioning

The Multidimensional Pain Inventory (MPI) measures the psychosocial impact of chronic pain [42]. The MPI has proven reliability and construct validity [43].

#### Negative Affect

Depressive symptoms and pain catastrophizing are key components of negative affect [44]. The Center for Epidemiologic Studies-Depression scale provides a validated measure of depressive symptoms [45] in patients with chronic pain [46,47]. The Pain Catastrophizing Scale provides a measure of negative cognitions and emotions associated with actual or anticipated pain experiences [48].

#### Baseline Smoking Status

Baseline smoking status was assessed using the techniques used by the Behavioral Risk Factor Surveillance System: (1) Have you ever smoked a cigarette, even a puff? (Yes or No); (2) Have you smoked at least 100 cigarettes in your entire life? (Yes, No, or Not sure); and (3) Do you now smoke cigarettes every day, some days, or not at all? (Every day, Some days, or Not at all) [49].

#### Quantitative Sensory Testing

Heat pain perception was quantified using the Computer Aided Sensory Evaluator IV (WR Electronics). This quantitative sensory testing device is validated [50-52], and we have used it to quantify opioid-induced hyperalgesia [15,16] and to study other pain-related states associated with altered heat pain perception [53-56].

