#### Study Participants

A total of 780 patients were approached for recruitment at each site (N=2340), and eligibility criteria for study participation are outlined in Textbox 1. Patients meeting these eligibility criteria were further categorized based on CONSORT criteria [5]. Criteria for the long-term CONSORT category included episodes of opioid prescribing lasting longer than 90 days and including 120 or more total days of supply or 10 or more prescriptions [5]. Criteria for the episodic CONSORT category included episodes lasting 90 days or longer, with total days of supply being fewer than 120 and the total number of prescriptions filled being fewer than 10. Criteria for the short-term CONSORT category included episodes of opioid prescribing lasting 90 days or fewer [5]. Although study participation was limited to adults who own a smartphone, recent data from January 2018 demonstrated 77% of US residents own a smartphone [10].

Eligibility criteria.

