#### Timeline for Establishing Consortium to Study Opioid Risks and Trends Criteria for Opioid Use

The timeline of the study was governed, in part, by the temporal requirements for applying CONSORT criteria (Figure 2). The beginning date of an episode of opioid use was defined as the date that the initial prescription was issued, with no previous opioid prescriptions issued for the preceding 6-month time period. The end date of an episode was the date that the last dispensed medication supply was exhausted, based on the days of supply as documented in the prescription instructions with no opioid dispensing in the ensuing 6 months. Patients who continued to use opioids on day 90 following issuance of the initial opioid prescription were invited to participate in the study assessment. Although it was not possible to accurately apply CONSORT criteria for episodic or long-term use on day 90, the study assessment was performed at this time point to ensure patients were captured at the earliest stages of episodic or long-term use. The status of opioid use in these patients was monitored every month by reviewing the EHR. This approach to follow-up limits the time interval between establishment of CONSORT criteria for episodic or long-term use and the final study assessment.

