**Figure 2 figure2:**
[figure not shown]
Flow diagram for establishing Consortium to Study Opioid Risks and Trends (CONSORT) criteria for opioid use.

A randomly selected group of patients meeting criteria for short-term use at day 90 were invited to participate in the study assessment. This group of patients was selected to be time-matched 1:1 to patients continuing to use opioids at day 90 (initial issue date ±2 weeks) Although it was not possible to accurately apply CONSORT criteria for short-term use until month 6 following issuance of the last prescription, the study assessment was performed at this time point to ensure that patients were captured in the earliest stages of short-term use. Because it was anticipated that the majority of the cohort would meet criteria for short-term use, it was not feasible to invite all patients to participate in the study assessment.

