#### Study Assessments

Assessments were performed at 2 time points: 3 months following dispensing of the initial opioid prescription and 9 months following dispensing of the initial opioid prescription.

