#### Data Analysis Plan

The primary research question for specific aim 1 was to identify patient characteristics associated with UPOU. A case-control design was used with controls time matched to cases. The expectation was that multiple patient characteristics would be associated with UPOU. Descriptive statistics (means, medians, and ranges) were generated to compare cases and controls on all patient characteristics. Differences in patient characteristics between cases and controls were assessed using bivariate tests including the McNemar test for categorical variables and paired 2-tailed *t* tests (or Wilcoxon signed rank test, if needed) for continuous variables. The results of the bivariate analyses were used to select variables for conditional logistic regression analyses to regress UPOU on all variables identified as potentially associated with the UPOU. The regression models were constructed in stages by incorporating predictors in conceptual blocks and using standard selection methods to retain variables. All models included a fixed effect for site. ORs and 95% CI were used to evaluate the magnitude and statistical significance of the association between predictors and outcome.

### Specific Aim 2

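### The heat pain contrast between cases and controls mixes any pre-existing pain sensitivity with the effects of the opioid use that defines the cases, so it cannot be read as a predictor of UPOU

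*Protocol article*

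**What the plan says.** All references are to the protocol article.

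- **Cases.** The section on the timeline for CONSORT criteria states: "Patients who continued to use opioids on day 90 following issuance of the initial opioid prescription were invited to participate in the study assessment".
- **Controls.** The text after Figure 2 states: "A randomly selected group of patients meeting criteria for short-term use at day 90 were invited to participate in the study assessment". Study Participants defines the category: "Criteria for the short-term CONSORT category included episodes of opioid prescribing lasting 90 days or fewer".
- **Matching.** "This group of patients was selected to be time-matched 1:1 to patients continuing to use opioids at day 90", with a window of 2 weeks either side of the initial issue date. No other matching factor is named.
- **Timing.** Study Assessments gives two time points, 3 and 9 months after the initial prescription was dispensed. No assessment before opioid exposure is described.
- **Measure.** Quantitative Sensory Testing says of the heat pain device: "we have used it to quantify opioid-induced hyperalgesia".
- **Opioid exposure data.** Verification of Opioid Status and Dose provides for conversion to daily morphine equivalents and adds: "The opioid status was biochemically verified with a urine toxicology screen".
- **Analysis.** The Aim 1 Data Analysis Plan states: "Descriptive statistics (means, medians, and ranges) were generated to compare cases and controls on all patient characteristics". Paired tests follow, and their results select variables for conditional logistic regression. The one adjustment named for every model is site. SEM Analysis says that the Aim 1 results feed the structural equation models.
- **Intended use.** The Conclusions foresee flagging at-risk patients in the health record when they receive their initial opioid prescription.

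**The concern.** Continuing opioid use is what separates a case from a control at day 90, and heat pain perception can respond to opioid use. The article says as much by introducing the device through hyperalgesia caused by opioids. With no measurement before exposure, a difference between the groups has at least two sources that the pooled comparison cannot tell apart:

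1. a difference in pain sensitivity that was there before the first prescription;
2. the effect of the opioid itself, whether analgesia from a recent dose, hyperalgesia from sustained exposure, or heightened sensitivity during withdrawal.

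The second source contains effects of opposite sign. It can produce a significant difference where no pre-existing one exists, or hide one that does. This matters for the stated use: a contrast generated by being on opioids at month 3 says nothing about an opioid-naive patient at the initial prescription. If heat pain passes the bivariate screen, the mixed quantity is also carried into the regression and structural equation models.

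**Working it through.** **1. The plan's own figure.** Inputs from Sample Size Estimates (Aim 1): 600 cases, 600 controls, power 0.8, two-sided alpha 0.05, exposure prevalence 0.5 in controls, zero correlation, detectable odds ratio 1.38.

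Dupont's matched-pair formula at OR = 1.38:
- exposure in cases p1 = 1.38 × 0.5 / (1 + 0.5 × 0.38) = 0.580
- probability that a pair is discordant = 0.580 × 0.5 + 0.420 × 0.5 = 0.5
- PA = 1.38 / 2.38 = 0.580
- discordant pairs = [1.96/2 + 0.842 × √(0.580 × 0.420)]² / (PA − 0.5)² ≈ 305.5
- total pairs = 305.5 / 0.5 ≈ 611

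Solved at exactly 600 pairs, the odds ratio is 1.384. The other two stated values also reproduce: 1.475 against 1.48 (r = 0.3), and 1.548 against 1.55 (r = 0.3, prevalence 0.7). The sample size is not in dispute. It only sets the scale for what follows.

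**2. What the paired test can detect.** Smallest difference with 80% power, in SD units: (1.96 + 0.842) × √(2(1 − r)/n).
- 600 pairs: 0.162 (r = 0), 0.135 (r = 0.3)
- 513 pairs, the number of cases recruited in Table 1: 0.175 (r = 0), 0.146 (r = 0.3)

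**3. What a drug-related shift alone would do.** Let d be the net shift in SD units caused by opioid exposure, with no pre-existing difference. By the normal approximation to the paired t test, λ = d√n / √(2(1 − r)), and the chance of a significant result is Φ(λ − 1.96) + Φ(−λ − 1.96). For 600 pairs and r = 0, λ = 17.32d. For example, d = 0.10 gives λ = 1.73 and 41%.

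The documents give no value for d or r. The values below are assumptions.

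| Assumed net shift d (SD) | 600 pairs, r = 0 | 600 pairs, r = 0.3 | 513 pairs, r = 0 |
|---|---|---|---|
| 0 | 5% | 5% | 5% |
| 0.05 | 14% | 18% | 13% |
| 0.10 | 41% | 54% | 36% |
| 0.15 | 74% | 87% | 67% |
| 0.20 | 93% | 98% | 89% |
| 0.30 | >99% | >99% | >99% |

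**4. The same on the odds-ratio scale.** With heat pain split at the control median, a shift of 0.20 SD gives Φ(0.20)/(1 − Φ(0.20)) = 0.579/0.421 = 1.38. That equals the smallest odds ratio the study was sized to detect.

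**5. Not every case on drug.** If half the cases have opioid on board and the effect in them is 0.30 SD, the net shift is 0.5 × 0.30 = 0.15 SD, which gives 74% (600 pairs, r = 0).

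**6. The opposite error.** Suppose a true difference of 0.162 SD, detectable with 80% power, is offset by a drug effect of 0.10 SD in the other direction. The net difference is 0.062 SD, λ = 17.32 × 0.062 = 1.07, and power falls to about 19%.

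**The case against.** **The article is condensed.** Quantitative Sensory Testing is two sentences long, and a full protocol or testing manual could fix testing relative to the last dose or specify covariates. That is fair, and no fault is found here with the absence of dose timing. But selection on continuing use, the two post-exposure time points and the comparison on all characteristics are stated in the article. Standardised timing would not make current users comparable with people who have stopped.

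**Aim 1 asks only for association.** SEM Analysis openly counts withdrawal and craving among patient characteristics, so a state measure is not out of place there. This supports keeping the contrast as description. It does not support reading it as a predictor at the initial prescription, which is the use that the Conclusions foresee.

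**Heat pain is one instance of a wider timing problem.** Withdrawal, craving and pain intensity are also measured after case status emerges. That is true. Heat pain deserves separate mention because the article itself ties the device to an opioid effect, and because urine results and dose allow a partial remedy.

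**The size has no anchor.** This stands. The effect and the share of cases on drug are not given. Expected rates of 20% episodic and 7% long-term use make about 74% of cases episodic (0.20/0.27), and Limitations says status rests on prescriptions issued. Many cases could be drug-free when tested, and opposing effects could net to nearly zero.

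**Stronger readings a reader might infer.** One is that the distortion is specifically an acute dose effect. The documents do not support that: the phrase about the device concerns hyperalgesia, which need not be acute. Another is that urine-negative cases give a clean comparison of underlying sensitivity. They do not, because they are a selected subset and may carry longer-lasting opioid effects.

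**Conclusion.** The concern holds as a limit on interpretation that can be partly repaired. As planned, the pooled heat pain contrast cannot separate pre-existing sensitivity from effects of current or recent opioid exposure, and matching on issue date does not help. The structure follows from the text. The size does not: the range of about 14% to over 99% significant results rests on an assumed net shift of 0.05 to 0.30 SD, 600 uncorrelated pairs and no true difference. Direction is unknown.

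A reader might conclude that heat pain must be dropped from the analysis, or that adjusting for current use or dose would settle the matter. The documents do not require the first, since the measure is legitimate as a description of cases. The second would not work, because current use largely coincides with case status.

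**What to change.** 1. Keep the pooled case-control comparison of heat pain as descriptive, and state that it cannot be read as a pre-existing predictor of UPOU.
2. From the urine results and doses already collected, add:
   - an off-drug sensitivity comparison of urine-opioid-negative cases with their matched controls;
   - urine-positive cases shown separately;
   - the within-case association of heat pain with daily morphine equivalents.
3. Enter heat pain in the conditional logistic and structural equation models only with this sensitivity analysis reported beside it.

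This assumes that the urine result comes from the same assessment as the heat pain test. The article implies this by listing both among the assessments but does not say so. Time since last dose is not listed as collected, so the proposal does not depend on it.

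**Cost.** No new data are needed, but the change goes beyond wording. Patient Recruitment says that the patient-characteristics analysis is complete, so a modest re-analysis is required. The structural equation models are still in development and can take the change now. The off-drug comparison uses fewer cases and is less precise. Because urine-negative cases are selected and may retain opioid effects, it reduces the mixing but does not remove it.

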#### Concomitant Treatments

Use of concomitant treatments for pain were assessed (eg, nonopioid medications, supplements, acupuncture, physical therapy, and chiropractic).

#### Sample Size Estimates

Based on our preliminary work [3,9,57-62], we estimated the rate of episodic opioid use would be 20% and the estimated rate of long-term use would be 7%. This would yield approximately 200 (780 × .27 = 210.6) patients developing some form of UPOU at each site. The analysis for specific aim 1 involved examining a wide variety of predictors of UPOU rather than 1 specific exposure. As a result, the minimum detectable odds ratios across a range of sample sizes were calculated. Setting the power at 0.8 and α at .05 (2-tailed), a total sample size of 1200 (600 cases and 600 controls) allowed detection of an odds ratio of 1.38 with a predictor that had a prevalence of 0.5 in controls and zero correlation in exposure between cases and controls. The detectable odds ratio (OR) goes up as the correlation between cases and controls becomes positive (detectable OR=1.48 with *r*=0.3), and it also increases as the prevalence of the exposure in the control group increases (detectable OR=1.55 with *r*=0.3 and prevalence of exposure=0.7 in controls).

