#### SEM Analysis

The primary goal of aim 3 was to combine the results from aims 1 and 2 and extend these by building a statistical model that synergistically integrated the three domains of the UPOU conceptual framework. The UPOU framework has a number of complexities that limit the use of regression including multiple correlated predictors and outcomes, unobserved constructs that are difficult to directly measure, and nesting of patients with clinicians who are nested within sites. SEM can estimate latent variables and include them as both exogenous and endogenous variables in the same model, use multiple observable and quantifiable indicators to estimate latent variables from the shared variability of these indicators, and accommodate multiple endogenous variables (ie, dependent variables or outcomes) in 1 model. Multilevel SEM can estimate latent variables at 1 or more levels (eg, patient and clinician levels) and appropriately test associations at and across these different levels for categorical and continuous outcomes.

The SEMs were developed in several steps. The number of measurement models were estimated for all constructs that potentially used latent variables. Descriptive statistics were examined including means, medians, SDs, ranges, measures of central tendencies, and normality of the distributions. Extensive preliminary analyses were conducted to evaluate possible inconsistencies in the data, outliers, and variations in the data, and clinically and statistically relevant cutoff points that may facilitate the analyses were identified. The primary outcome measure was UPOU, measured as a dichotomous variable of cases and time-matched controls. The predictors of interest were grouped into 3 domains: patient characteristics, practice environment, and clinician characteristics. Each of these domains contained a number of directly observable and directly unobservable constructs. Examples of directly observable variables in the patient characteristic domain included age, sex, and employment status. Examples of directly unobservable constructs in the patient characteristic domain included symptoms of opioid withdrawal, opioid craving, and the psychosocial impact of chronic pain. Analyses (eg, coefficient α, principal components analysis, and factor analysis) were conducted to determine how to optimally combine scale items into reliable measures.

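### The Aim 1 detectable odds ratios (1.38, 1.48, 1.55) are right for one predictor tested alone, but power at those values is below 80% for correlated predictors in the multivariable model used to judge significance

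*Protocol article*

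**What the plan says.** Specific Aim 1, Sample Size Estimates, sets the terms: "Setting the power at 0.8 and α at .05 (2-tailed"), with "a total sample size of 1200 (600 cases and 600 controls"). This size "allowed detection of an odds ratio of 1.38 with a predictor that had a prevalence of 0.5 in controls" when exposure is uncorrelated between a case and its control. The section adds 1.48 for a case-control correlation r of 0.3, and 1.55 for r of 0.3 with a control prevalence of 0.7. It allows for no other correlation.

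Matching is described under the timeline for the CONSORT criteria: "This group of patients was selected to be time-matched 1:1 to patients continuing to use opioids at day 90".

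Specific Aim 1, Data Analysis Plan, has two steps. Cases and controls are first compared on each characteristic with McNemar and paired tests. Those results then select variables for conditional logistic regression, "to regress UPOU on all variables identified as potentially associated with the UPOU", built in blocks with selection methods and a site effect. The closing sentence is: "ORs and 95% CI were used to evaluate the magnitude and statistical significance of the association between predictors and outcome".

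On the predictors, the SEM Analysis section lists complexities of the framework "including multiple correlated predictors and outcomes". The Negative Affect section says: "Depressive symptoms and pain catastrophizing are key components of negative affect". Misuse is covered by three instruments, and pain by several scales.

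The Limitations section states that the sample target was largely reached and that target power was therefore met.

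**The concern.** The sample size section describes the sensitivity of a one-predictor comparison. The section after it takes its conclusions from adjusted odds ratios in a model with several predictors. When a predictor overlaps with others in the model, its adjusted log odds ratio has a larger variance, so the same true odds ratio is detected less often. The r in the sample size section does not cover this. It is the correlation of one exposure between the two members of a pair, not the correlation between different predictors in the same person.

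At stake is how negative results are read. Someone relying on 1.38 and on the Limitations statement could take a non-significant adjusted odds ratio as good evidence that a characteristic does not matter, when power for an effect of that size may have been well short of 80%.

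**Working it through.** **Inputs from the article.** Two-sided α 0.05; power 0.80; 600 matched pairs (1:1); control prevalence p0 of 0.5 or 0.7; case-control correlation r of 0 or 0.3. Table 1 gives 513 cases and 517 controls, so at most 513 pairs at 1:1.

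**Assumption.** R², the share of a predictor's variance explained by the other predictors in the model. The article gives no value; 0.1 to 0.5 is shown.

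**Step 1: reproduce the printed values.** Matched case-control formula for one binary exposure:

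- p11 = p1·p0 + r·√(p1·q1·p0·q0), where q = 1 − p
- OR = (p1 − p11)/(p0 − p11)
- m = N × (p1 + p0 − 2·p11), the expected discordant pairs
- power = Φ{[√m·(π − 0.5) − 1.96 × 0.5] / √(π(1 − π))}, with π = OR/(1 + OR)

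For OR 1.38, p0 = 0.5 and r = 0: π = 1.38/2.38 = 0.5798 and m = 600 × 0.5 = 300. Power = Φ[(17.32 × 0.0798 − 0.98)/0.4936] = Φ(0.816) = 0.793.

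| Setting | Printed OR | Recomputed OR at 80% power | Power at printed OR |
|---|---|---|---|
| p0 0.5, r 0 | 1.38 | 1.384 | 0.793 |
| p0 0.5, r 0.3 | 1.48 | 1.475 | 0.807 |
| p0 0.7, r 0.3 | 1.55 | 1.548 | 0.802 |

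The printed values are correct, and they contain no allowance for other predictors.

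**Step 2: allow for adjustment.** The variance of the log odds ratio grows by about 1/(1 − R²), so N is replaced by N(1 − R²). Example with R² = 0.3: m = 300 × 0.7 = 210, and power at 1.38 = Φ[(14.49 × 0.0798 − 0.98)/0.4936] = Φ(0.358) = 0.64.

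Power at the printed OR, 600 pairs, all covariates kept in:

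| R² | OR 1.38 | OR 1.48 | OR 1.55 |
|---|---|---|---|
| 0.1 | 0.75 | 0.76 | 0.76 |
| 0.2 | 0.70 | 0.71 | 0.71 |
| 0.3 | 0.64 | 0.66 | 0.65 |
| 0.5 | 0.50 | 0.51 | 0.51 |

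At R² = 0.05 the loss is only about 2 points.

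Adjusted OR detectable at 80% power, R² from 0.1 to 0.5:

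| Setting | 600 pairs | 513 pairs |
|---|---|---|
| p0 0.5, r 0 | 1.41 to 1.59 | 1.45 to 1.65 |
| p0 0.5, r 0.3 | 1.51 to 1.74 | 1.56 to 1.82 |
| p0 0.7, r 0.3 | 1.59 to 1.88 | 1.65 to 1.98 |

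**Step 3: check by simulation.** Conditional logistic regression, 600 pairs, adjusted OR 1.38, 1,500 replicates. Power was 0.77 with no covariates, 0.69 to 0.75 with five covariates at R² about 0.14, and 0.58 to 0.65 with five at R² about 0.27. This agrees with the direction and rough size of Step 2.

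**Step 4: effect of variable selection.** With five correlated covariates that have no effect of their own (R² about 0.27, OR 1.384, 800 replicates), power was 0.65 with all covariates forced in. It was 0.73 after an assumed screen at p<.10 and backward selection at p<.05. When the covariates had effects of their own, the selected model gave 0.66 to 0.76. Selection reduces the loss but does not remove it. The thresholds are assumptions, since the article names only standard methods.

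**The case against.** The strongest reply is that nothing is miscalculated. The sample size section states its conditions: one predictor, a given prevalence, a given case-control correlation. It makes no claim about adjusted odds ratios. The McNemar tests are themselves a planned assessment of case-control differences, and the Aim 1 question asks which characteristics are associated with UPOU, not independently associated. All of this stands. A reader might infer that 1.38 is an arithmetic error, or that the bivariate tests serve only as a screen; the article supports neither.

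It can also be said that the size of the loss is unknown, that the remark on correlated predictors concerns the whole framework and is given as a reason for SEM, and that the planned selection would drop some redundant covariates. This stands too, and it limits what can be claimed about magnitude.

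Finally, the 95% CIs show the precision of each adjusted estimate directly, and no section says that a non-significant result will be read as no association. That lessens the practical harm. It does not reconcile the sections: specific detectable odds ratios are printed, a different analysis is fixed for judging significance, and the Limitations section relies on the stated power. Because these are all statements in the article, the point is not about detail left to a fuller document.

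**Conclusion.** The point holds in a conditional form. The three printed odds ratios are correct for an unadjusted comparison of one binary predictor in 600 pairs. For any predictor materially correlated with those retained in the regression, the analysis that decides significance has less than 80% power at those values. With 600 pairs and all covariates kept in, power at 1.38 is about 75% at R² = 0.1 and about 50% at R² = 0.5.

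A reader might go further and conclude that the stated 80% is missed for every predictor, or that 50% is the expected power. The documents do not support that. A predictor with R² below about 0.05 keeps roughly 80%, no R² is reported, and selection may recover part of the loss.

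Separately from adjustment, with at most 513 pairs the unadjusted power at 1.38 is already about 73%. The Limitations statement on power therefore needs qualifying on both counts.

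**What to change.** - In Aim 1, Sample Size Estimates, label 1.38, 1.48 and 1.55 as unadjusted single-predictor values.
- Beside them, give adjusted detectable odds ratios for an assumed R² of 0.1 to 0.5, using the ranges tabulated above for the planned 600 pairs and for at most 513 pairs. State that all covariates are taken as kept in the model.
- In Limitations, qualify the statement that target power was met: the target refers to unadjusted comparisons at the planned size.
- When reporting Aim 1, interpret non-significant adjusted odds ratios by their 95% CIs rather than against 1.38.

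The cost is a short recalculation and some wording. No patients are added and no analysis changes; the stated sensitivity becomes less favourable.
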